#### Control Group

2.10.2

For the control group, routine care will be done (Routine care means receiving standard treatments by a gynecologist and balanced physical activity and diet).

Questionnaires will be done simultaneously with the intervention group at all stages.

Participants' records will be organized numerically and kept in a secure, easily accessible way and location. Records of participants will be maintained for 2 years following the conclusion of the study.

### Protocol Deviation

2.11

Deviations or protocol violations may have occurred in this study and will be reported. An instance of deviation in a procedure is a follow‐up appointment occurring at a slightly varied time frame than mandated by the protocol; patients with these deviations will be incorporated into the intention‐to‐treat analysis. All study subjects randomly assigned to the studied groups during randomization processes, regardless of the type of intervention received during the study, their violation of protocol, discontinuation, and withdrawal from participating in the study, as well as all cases that occurred after randomization, will be included in the intention‐to‐treat analysis.

### Modification to the Protocol

2.12

Any modifications to the procedure that could influence the study's execution, the patient's potential benefit, or the patient's safety, such as alterations in study objectives, design, patient population, sample size, study methods, or important administrative elements, will necessitate official documentation. This modification will be concurred by the research team and sanctioned by the Ethics Committee.

### Statistical Analysis

2.13

The data from quantitative variables will be described by calculating the mean ± standard deviation, and qualitative variables will be described in terms of frequency and percentage. To compare variables between intervention and control groups according to the qualitative and quantitative variable nature, the *χ*
^2^ test (if the default is not established, Fisher's exact test) and *t*‐test of two independent samples, analysis of variance, or its non‐parametric equivalent (Mann–Whitney and Kruskal–Wallis) will be used, respectively. It should be noted that checking the defaults in terms of normality (Kolmogorov–Smirnov and Shapiro–Wilk test) and equality of variances (Levene and F test) will be on the agenda. Finally, to compare the mean resilience score between the two intervention and control groups during the study period (before the intervention, right after the intervention, and 4 weeks post‐intervention), and also to control for the effect of intervening factors, repeated measures ANOVA or mixed models will be used for variance analysis. For every outcome, the projected effect size along with its 95% confidence interval will be displayed. The significance level of the tests will be 0.05. The analysis will be conducted using SPSS V.26. The reporting of statistical results will adhere to the Statistical Analyses and Methods in the Published Literature (SAMPL) guideline [53].

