### Objectives

2.1

The primary objective of this study is to assess the impact of hypnotherapy on the resilience of individuals suffering from polycystic ovary syndrome (PCOS). The particular aims of this study are to assess and contrast the levels of resilience, quality of life, anxiety, and depression in both the control and intervention groups before the intervention, right after the intervention, and 4 weeks post‐intervention.

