#### Sample Size

2.5.1

According to Fathi et al.'s study [41], the average resilience in the control group was 48.17 ± 20.61, and in the intervention group was 69.80 ± 23.38. By applying these findings and taking into account a type 1 error of 0.05 and a test power of 0.90, the sample size for every group was calculated using the following formula:

Therefore, 22 people in each group and a total of 44 people will enter the study. But considering that in this study, resilience is measured in three stages (before the intervention, right after the intervention, and 4 weeks post‐intervention). The samples may have dropped. For this problem, the final sample volume was determined with a 20% drop:

The total sample size was 55, considering the 20% attrition, and as regards, we have two groups, so we considered the total sample size to be 56 people. Therefore, 28 samples are included in the study in each group (intervention and control).

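### Quality of life, anxiety and depression have no stated analysis that uses their baseline scores, and the scale of their promised effect size is left open

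*Protocol article*

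**What the plan says.** All references are to the protocol article.

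- **Outcomes and timing.** Objectives (2.1) sets out to contrast "levels of resilience, quality of life, anxiety, and depression in both the control and intervention groups before the intervention", right after it, and 4 weeks later. Data Collection Tools (2.9.1) makes resilience primary, and PCOSQ quality of life and HADS anxiety and depression secondary.
- **Generic comparison.** Statistical Analysis (2.13) compares quantitative variables between groups by a two-sample t-test or ANOVA, or by Mann–Whitney or Kruskal–Wallis. No baseline term is mentioned.
- **Preliminary checks.** The next sentence begins "It should be noted that checking the defaults in terms of normality" and names Kolmogorov–Smirnov and Shapiro–Wilk, then Levene and F tests for equal variances.
- **Longitudinal model.** Repeated measures ANOVA or a mixed model, also meant to control for other factors, is to be used "to compare the mean resilience score between the two intervention and control groups during the study period". No other outcome is named for it.
- **Reporting.** "For every outcome, the projected effect size along with its 95% confidence interval will be displayed". The scale of that effect size is not named.
- **Covariates.** The section on potential confounders (2.15) adjusts only for variables found to differ significantly between the groups.

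**The concern.** Three of the four outcome scores are measured at baseline, yet the article states no analysis that uses those values. A baseline score usually predicts the follow-up score, so leaving it out widens the interval for the treatment effect. That matters here because the trial is small and was sized on resilience alone, so the secondary outcomes have no planned power.

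The second issue is what is being estimated. If the checks decide between a t-test and a rank test, one outcome or time point may be analysed as a mean difference and another as a rank comparison, depending on the sample. An effect size with an interval is promised for every outcome, but the text does not say which of these it will be.

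**Working it through.** **1. The plan's own sample size.** Inputs from Sample Size (2.5.1): "the average resilience in the control group was 48.17 ± 20.61, and in the intervention group was 69.80 ± 23.38", "taking into account a type 1 error of 0.05 and a test power of 0.90", and "the final sample volume was determined with a 20% drop".

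- Difference: 69.80 − 48.17 = 21.63.
- Pooled SD: √((20.61² + 23.38²)/2) = 22.04, so d = 21.63/22.04 = 0.98.
- n per group = 2 × ((1.960 + 1.282) × 22.04/21.63)² = 21.8, so 22 (two-sided; a one-sided test would give 18).
- Dropout: 44/0.8 = 55, raised to 56. "Therefore, 28 samples are included in the study in each group (intervention and control").

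The stated figure reproduces. It rests on resilience only. The relevant range for the secondary scores is 22 (after the planned dropout) to 28 per arm.

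**2. Power with and without the baseline score.** Assumptions, because the documents give neither: a true effect of 0.5 SD at one follow-up, and a baseline to follow-up correlation r of 0.3 to 0.7. Adjustment multiplies the residual variance by 1 − r², so the effective standardised effect is 0.5/√(1 − r²). Power is from the noncentral t distribution with 2n − 2 degrees of freedom, noncentrality (effective effect) × √(n/2), two-sided 5%. The one degree of freedom spent on the covariate changes the results by less than 0.1 percentage point.

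| Analysis | Effective effect | Power, 22 per arm | Power, 28 per arm |
|---|---|---|---|
| Unadjusted | 0.500 | 36.7% | 45.1% |
| r = 0.3 | 0.524 | 39.7% | 48.7% |
| r = 0.4 | 0.546 | 42.4% | 51.8% |
| r = 0.5 | 0.577 | 46.5% | 56.4% |
| r = 0.6 | 0.625 | 52.6% | 63.2% |
| r = 0.7 | 0.700 | 62.1% | 73.0% |

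A normal approximation at 22 per arm agrees closely: 38% unadjusted, then 41%, 48% and 64% at r = 0.3, 0.5 and 0.7.

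**3. How often the checks would change the test.** The article gives no threshold and does not say which check governs, so a rule was assumed: Shapiro–Wilk in each arm at 0.05, with or without Levene at 0.05, switching to Mann–Whitney on any failure. There were 4,000 simulated null trials per scenario.

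| True distribution | n per arm | Shapiro–Wilk alone | With Levene | Type I error (with Levene) |
|---|---|---|---|---|
| Normal | 22 | 10% | 15% | 5.5% |
| Normal | 28 | 11% | 15% | 5.3% |
| Gamma, shape 4 | 22 | 54% | 58% | 5.0% |
| Gamma, shape 4 | 28 | 67% | 70% | 5.1% |
| Gamma, shape 2 | 22 | 83% | 85% | 5.1% |
| Gamma, shape 2 | 28 | 92% | 93% | 4.3% |

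A separate run of 8,000 null trials with Shapiro–Wilk alone at 22 per arm gave type I error of 5.0%, 6.0% and 6.1% for the three distributions. Across all runs the error rate stays near nominal.

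**4. Whether other text supplies the adjustment.** With two groups, ANOVA and Kruskal–Wallis are equivalent to the t-test and Mann–Whitney and are equally unadjusted. The confounder section would bring in a baseline score only after a significant baseline difference, which is a data-dependent step and not planned adjustment.

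**The case against.** The generic sentence names none of the secondary outcomes, and its pairing with χ² and Fisher shows that it covers qualitative variables too. It could be read as a rule for baseline and descriptive comparisons, with the secondary-outcome model left to a full plan that is not shown. That reading is possible. But it would leave three named outcomes with no stated analysis at all, and the Abstract gives the same generic comparison as the analysis method. The article also ties its longitudinal model to resilience by name.

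The switching rule is implied, not written. This is fair: the checks follow directly on the mention of a non-parametric equivalent, and the χ² clause uses a failed assumption as the trigger for Fisher's test, but no trigger is spelled out for the quantitative tests.

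A reader might infer three stronger claims, and none is supported:

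- **Pre-testing inflates the false-positive rate.** The simulations show no material inflation.
- **The choice of test is a coin toss.** That fits only one assumed distribution at 22 per arm. The switch rate depends on the skewness of PCOSQ and HADS scores, which the documents do not give.
- **The reported effect will change scale.** The article describes quantitative variables by mean and SD and nowhere says that the effect size follows the test. The scale is unnamed, and no more than that can be said.

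Finally, the precision gain rests on an assumed effect and correlation, is small at r = 0.3, and concerns outcomes for which the trial was not sized. All of that stands and limits the weight of the point.

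**Conclusion.** The point holds as lost precision and an unfixed effect measure for three secondary outcomes. As written, PCOSQ, HADS anxiety and HADS depression are compared without their baseline scores. Under an assumed 0.5 SD effect at 22 per arm, power is 37% where baseline adjustment would give 40% to 62%. The upper part of that range needs a correlation near 0.7.

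How often the test would switch cannot be known from the documents: about 10% (Shapiro–Wilk alone) for normal data, and over 80% for clearly skewed data. Resilience has its own longitudinal model and is not affected in the same way. The change is worth making because the baseline data are already collected and the model type is already named, but it is not an error in the validity of the tests.

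**What to change.** In Statistical Analysis (2.13), extend the mixed model to PCOSQ, HADS anxiety and HADS depression at both follow-ups. Terms: baseline score, the stratification factors from Random Allocation (marital status and BMI class), group, time, and group by time. Fit it whatever the normality and variance tests show, and remove those tests as a basis for choosing the analysis of the score outcomes. Name the effect measure: the adjusted mean difference at each follow-up with its 95% interval, using a bootstrap interval if residuals are skewed. Keep Mann–Whitney as a stated sensitivity analysis. Use the same baseline-adjusted form for resilience, for consistency.

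Cost: no extra participants, visits or measurements, and the article already names mixed models and SPSS V.26. For a strongly skewed score a rank test can have more power, which the sensitivity analysis would still show. Under Modification to the Protocol (2.12) the change must be documented, agreed by the research team and approved by the Ethics Committee. Because the article reports that recruitment is under way, this should be done before the analyst sees outcome data by group.

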### Testing of the Hypothesis

2.14

The main hypothesis of this study involves examining whether hypnotherapy significantly impacts the resilience of women with PCOS. The research is designed to measure changes in resilience levels before the intervention, right after the intervention, and 4 weeks post‐intervention.

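### No deciding contrast is named for resilience over three visits that include baseline, so the 0.90 power computed for one two-mean comparison is not assured

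*Protocol article*

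**What the plan says.** **Sample size (2.5.1).** One mean and SD per group are taken from a cited study: "the average resilience in the control group was 48.17 ± 20.61" and "in the intervention group was 69.80 ± 23.38". The calculation proceeds by "taking into account a type 1 error of 0.05 and a test power of 0.90" and concludes that "22 people in each group and a total of 44 people will enter the study". This is raised to 56 in total (28 per group) for 20% attrition. The section does not say at which visit the two means were measured.

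**Analysis (2.13).** The primary outcome is analysed by repeated measures ANOVA or mixed models, "to compare the mean resilience score between the two intervention and control groups during the study period". The period is spelled out as baseline, end of intervention and 4 weeks later. Control for intervening factors is mentioned, but baseline resilience is not named as a covariate. The same section provides two-sample t-tests or Mann–Whitney tests for comparing variables between groups in general, and adds: "The significance level of the tests will be 0.05".

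**Hypothesis (2.14).** The main hypothesis is an effect of hypnotherapy on resilience. "The research is designed to measure changes in resilience levels before the intervention, right after the intervention" and 4 weeks afterwards. No visit or contrast is singled out, and the objectives in 2.1 list the same three times with equal standing.

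**The concern.** A three-visit model gives several answers to the question of whether hypnotherapy changed resilience: a group main effect averaged over all visits, a group-by-time interaction, and a difference at each visit. They have different power and estimate different quantities. In a randomised trial the arms do not differ in expectation at baseline, so a main effect that averages over baseline shrinks the estimated difference.

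Two things are at stake. First, the trial may be judged on a test with clearly less than the stated power, and may report a diluted difference as its result. Second, if the choice is left until results are seen, the 0.05 level of the trial as a whole is no longer protected.

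**Working it through.** **Inputs from 2.5.1.** Means 48.17 and 69.80, SDs 20.61 and 23.38, alpha 0.05, power 0.90, 22 evaluable and 28 enrolled per arm.

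**Assumptions, because the protocol gives no figure.** Two-sided testing; equal correlation ρ between any two visits, set at 0.3, 0.5 and 0.7; no difference at baseline and, unless stated otherwise, the full difference at both later visits.

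**Step 1: the plan's own figure.**
- Difference: 69.80 − 48.17 = 21.63.
- SD: √[(20.61² + 23.38²)/2] = 22.04.
- Standardised difference: d = 21.63/22.04 = 0.981.
- n per arm: 2(1.960 + 1.282)²/d² = 21.8, rounded up to 22. A one-sided test would give 18, so two-sided matches the plan.
- Attrition: 44/0.80 = 55, made even at 56.

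The stated sample size is reproduced. Power at 22 per arm is 0.902 by the normal approximation and 0.889 by the noncentral t.

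**Step 2: group main effect over three visits.** The estimated difference is (0 + 21.63 + 21.63)/3 = 14.42. The variance of a patient's three-visit mean is SD²(1 + 2ρ)/3. The standardised effect is therefore (2/3)d/√[(1 + 2ρ)/3], and the noncentrality is that value times √(n/2).

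**Step 3: group-by-time test.** Noncentral F with 2 and 4(n − 1) degrees of freedom and λ = (n/2)(2/3)d²/(1 − ρ). At n = 22, λ is 10.1, 14.1 and 23.6.

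**Step 4: baseline-adjusted difference at one later visit.** Standardised effect d/√(1 − ρ²) = 1.029, 1.133 and 1.374.

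| Power | ρ = 0.3 | ρ = 0.5 | ρ = 0.7 |
|---|---|---|---|
| Main effect: standardised size | 0.896 | 0.801 | 0.732 |
| Main effect, 22 per arm | 0.83 | 0.74 | 0.66 |
| Main effect, all 28 per arm retained | 0.91 | 0.84 | 0.77 |
| Group-by-time, 22 per arm | 0.80 | 0.92 | 0.99 |
| Baseline-adjusted, one visit, 22 per arm | 0.92 | 0.96 | 0.99 |
| Baseline-adjusted, mean of both later visits, 22 per arm | 0.99 | 0.99 | >0.99 |

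The last row uses d/√[(1 + ρ)/2 − ρ²].

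**Step 5: sensitivity to a fading effect.** Suppose the difference halves by 4 weeks, with 22 per arm.
- The main effect estimates (0 + 21.63 + 10.815)/3 = 10.815, with power 0.59, 0.50 and 0.43.
- The group-by-time test has 0.68, 0.82 and 0.97.
- A baseline-adjusted contrast at 4 weeks alone, with d/2 in Step 4, has 0.39, 0.45 and 0.61.
- The baseline-adjusted average of both later visits, with 0.75d, has 0.89, 0.92 and 0.98.

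**Step 6: false positives.** In 40,000 simulated null trials per correlation, with ρ from 0.3 to 0.8 and 22 per arm:
- main effect alone, or interaction alone: 0.049 to 0.052;
- either later-visit t-test counting as success: 0.078 to 0.097;
- main effect or interaction counting: about 0.10;
- any of these four tests counting: 0.12 to 0.15.

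**The case against.** The strongest reply is that the low power comes from a choice of reading. Section 2.13 names no effect within the model, and 2.14 speaks of changes in resilience. A hypothesis about change fits the group-by-time test, for which baseline is a needed reference and not a dilution. That test exceeds 0.90 with 22 per arm once the correlation is about 0.5 or more and the effect is sustained. This stands. A reader might infer that the stated 0.90 and 0.05 fail for all the planned tests, or that baseline as an outcome level is wrong in itself. The documents support neither.

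A reader might also infer that the plan carries a false-positive rate of 0.12 to 0.15. It does not. That rate needs a rule by which any of four tests counts as success, and the protocol states no such rule. The t-test sentence covers variables in general, and resilience over time is then assigned to the longitudinal model. The rate is a scenario only.

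Three further points stand. Section 2.5.1 does not say that its means are post-intervention values. With no attrition the main effect regains 0.91 at a correlation of 0.3, though not at 0.5 or 0.7. Recruitment has begun, so the change needs the formal route in 2.12.

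It can also be said that model terms belong in a statistical analysis plan, which is not shown and may name the contrast. This weakens the point but does not remove it. The protocol does state a primary analysis, and its wording admits a reading that does not deliver the power for which the trial was sized.

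**Conclusion.** The point holds in this form: the deciding contrast is open, and the 0.90 power was computed for a different, single comparison, so it is not assured. On the group-main-effect reading, a sustained difference of 21.63 is reported as 14.42. Power is then about 0.66 to 0.83 with 22 per arm, or 0.77 to 0.91 if all 28 are retained. On the group-by-time reading it is 0.80 to 0.99 with 22 per arm. The sample size arithmetic is correct, and each test taken alone keeps 0.05.

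These figures rest on the assumed correlations, equal correlation between visits, and an effect sustained at both later visits. The protocol supplies none of the three. This should be fixed, but it does not invalidate the design.

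**What to change.** In 2.13 and 2.14, replace the open choice of method for the primary outcome by one mixed model. Its outcomes are the two post-baseline CD-RIS scores; its fixed effects are arm, visit, arm-by-visit and baseline CD-RIS. Name one post-baseline contrast as primary at two-sided 0.05: either one visit chosen by the sponsor, or the average of both. Label the other contrasts and all t-tests or Mann–Whitney tests of resilience as supportive.

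The sponsor should weigh the likely course of the effect when choosing. A single-visit contrast reaches 0.92 or more with 22 per arm only if the full difference is present at that visit. The average of both visits is less sensitive to fading, but estimates an average effect.

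The baseline score is already collected, so no new data, visits or patients are needed. The cost is an amendment documented and approved under 2.12 while the data are still blinded, and the loss of freedom to pick the visit or test afterwards.

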### Testing of the Hypothesis

2.14

The main hypothesis of this study involves examining whether hypnotherapy significantly impacts the resilience of women with PCOS. The research is designed to measure changes in resilience levels before the intervention, right after the intervention, and 4 weeks post‐intervention.

### Potential Cofounders

2.15

At the start of the research, various demographic and medical variables that could create bias will be documented. Additionally, both groups' participants will be required to continue their regular diet and exercise routine throughout the study. To guarantee that participants adhere to the protocol, their food consumption and exercise levels will be evaluated in each session and documented. Eventually, all possible confounders will be statistically examined, and if a significant difference is found between the groups, their impacts on study results will be modified.

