#### Hypnotherapy Intervention Group

2.10.1

In the intervention group, hypnotherapy is performed by a qualified researcher who is certified by the Iranian Association of Clinical Hypnosis and holds a valid credential. For every participant in the intervention group, there will be 6 weekly hypnotherapy sessions lasting 40–60 min each (Table 1).

**Table 1 hsr271608-tbl-0001:** The content of six hypnotherapy sessions.

Sessions	The subject matter of the session
First	Taking a history, fully explaining how to do the work, educating and preparing the patient, eliminating the misunderstanding of hypnosis, and completing the questionnaires (Patients are also asked to describe a place in the real world that gives them a sense of safety and comfort).
Second	Induction and deepening, and direct instincts to increase relaxation and conditioning for rapid hypnosis in the next sessions.
Third	Strengthening the ego to increase self‐esteem and increase the endurance and resilience to life issues in the individual.
Fourth	Age regression and dealing with negative emotions, and then increasing calmness.
Fifth	Age progression and conditioning to improve lifestyle.
Sixth	Reviewing the previous sessions, the mental experience of a favorable physical feeling, and focusing on increasing relaxation in the whole body and mind. Completing the questionnaires again.

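### The adjustment rule in section 2.15 is not limited to baseline variables, so it can take in diet and exercise recorded during treatment, which hypnotherapy may itself change

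*Protocol article*

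**What the plan says.** All references are to the Protocol article.

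- **Section 2.15 (Potential Cofounders)** begins with baseline data: "At the start of the research, various demographic and medical variables that could create bias will be documented". It then turns to conduct during the trial: "both groups' participants will be required to continue their regular diet and exercise routine throughout the study". To check adherence, and running straight on to the confounders, it says that "their food consumption and exercise levels will be evaluated in each session and documented. Eventually, all possible confounders will be statistically examined". It closes with the rule: "if a significant difference is found between the groups, their impacts on study results will be modified".
- **Section 2.13 (Statistical Analysis)** describes the comparison of mean resilience over the three time points: "and also to control for the effect of intervening factors, repeated measures ANOVA or mixed models will be used for variance analysis". It does not define the intervening factors.
- **Section 2.10.1, Table 1** gives the content of the fifth of six weekly hypnotherapy sessions: "Age progression and conditioning to improve lifestyle".
- **Section 2.10 (Interventions)** recommends a daily energy intake and a weekly amount of aerobic exercise to both arms during the study.
- **Sections 2.1, 2.9.1 and 2.14** make the effect of hypnotherapy on resilience the primary question.

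**The concern.** Diet and exercise recorded at the sessions are measured after randomisation. A variable measured then cannot confound a randomised comparison. It can, however, lie on the path from treatment to outcome, and Table 1 gives a reason to think so, because one hypnotherapy session is aimed at lifestyle.

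For such a variable the rule works in the wrong direction. Adjustment is triggered by a significant difference between arms, and that difference becomes more likely the more hypnotherapy changes lifestyle. Once the variable is in the model, the arm coefficient is the part of the effect that does not pass through lifestyle, whereas the stated objective is the whole effect. Precision also suffers, because the covariate is correlated with arm.

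This is separate from how baseline covariates are chosen. Pre-specifying the baseline covariates would not cure it while on-treatment variables remain eligible.

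**Working it through.** **1. Inputs from section 2.5.1.** Resilience is 48.17 (SD 20.61) in controls and 69.80 (SD 23.38) under intervention, with type 1 error 0.05 and power 0.90.

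- Difference d = 69.80 − 48.17 = 21.63
- Pooled SD = √((20.61² + 23.38²)/2) = 22.04
- n per arm = 2 × (22.04 × (1.960 + 1.282)/21.63)² = 21.8, rounded up to 22
- 44/(1 − 0.20) = 55, rounded up to 56, or 28 per arm

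The plan's sample size reproduces and is not affected by this point.

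**2. Assumptions, not in the documents.** Hypnotherapy shifts a lifestyle score by *a* SD, and a share *s* of the 21.63 points acts through that score. The model is a single post-treatment comparison with within-arm SD held at 22.04. The slope of resilience on the score is s × 21.63/a.

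**3. If the score is always in the model,** the expected estimate is (1 − s) × 21.63:

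- s = 15%: 0.85 × 21.63 = 18.4
- s = 30%: 0.70 × 21.63 = 15.1

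**4. Under the stated rule,** the score enters only when the arms differ at p < 0.05, so the mean estimate lies between these values and 21.63. Simulation at 22 per arm gives the results below; ranges show the spread over repeated simulations. Unadjusted, the estimate is 21.6 points and power 0.89.

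| Assumed shift | Trials in which the score enters | Mediated share | Mean estimate | Power |
|---|---|---|---|---|
| 0.8 SD | about 73% | 0 | 21.6 (no bias) | 0.82–0.83 |
| 0.8 SD | about 73% | 15% | about 19 | 0.73–0.74 |
| 0.8 SD | about 73% | 30% | about 16 | 0.62–0.64 |
| 0.3 SD | about 16% | 0 | 21.6 (no bias) | about 0.87–0.88 |
| 0.3 SD | about 16% | 15% | about 20.3–20.5 | about 0.86 |

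The 0.3 SD rows stop at 15% because 30% would need a within-arm correlation between lifestyle and resilience of (0.30 × 21.63/0.3)/22.04 = 0.98, which is not credible. At 0.8 SD and 30% the same formula gives (0.30 × 21.63/0.8)/22.04 = 0.37.

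**5. With all 28 per arm analysed,** a 0.8 SD shift triggers adjustment in about 84% of trials. At 30% mediated, the rule gives about 15.5 to 15.7 points, and power falls from 0.95 to 0.72. A larger sample raises power but triggers the adjustment more often, so the bias does not shrink.

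**6. The text on diet and exercise, side by side.** Section 2.10 recommends a set intake and activity level to both arms. Section 2.15 requires both arms to keep their regular routine. Table 1 has one arm conditioned to improve lifestyle. These three statements do not fit together as written.

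**The case against.** The strongest reply is that the protocol never says diet and exercise will be adjusted for. The variables it describes as able to create bias are those documented at the start. Diet and exercise are recorded to check adherence, and the closing sentence names no variable. A reading limited to baseline is available. This stands as a limit on certainty, and a reader who inferred that such adjustment is expressly planned would go beyond the text. It does not remove the point: the on-treatment records sit in the confounder section, immediately before a rule covering all possible confounders, with no restriction on timing. An analyst could follow that text and include them.

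Four further replies have weight:

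- **Lifestyle is not spelled out.** Table 1 does not say that it means diet or exercise. The session is the fifth of six, so most session records precede it, and both arms receive the same recommendation. A shift as large as 0.8 SD may therefore be too much, which is why 0.3 SD is shown beside it.
- **Intervening factors may be a loose word for confounders.** The phrase in 2.13 does not by itself show that on-treatment variables enter the model.
- **Control records are uncertain.** The only sessions the article schedules are hypnotherapy sessions. If controls have no comparable record, the test that triggers adjustment may not be feasible for these variables.
- **The calculation is simplified.** It uses one post-treatment comparison rather than the repeated-measures model of 2.13.

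Two stronger inferences should be avoided. The 18.4 and 15.1 points in step 3 are for adjustment in every trial, not for the rule as stated. And no passage says that a lifestyle change after session five would count as non-adherence; the statements conflict, but that consequence is not written.

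**Conclusion.** The point holds as a defect in how the rule is worded. Section 2.15 leaves on-treatment diet and exercise eligible for adjustment, on a trigger that hypnotherapy itself can set off, and 2.13 applies control of undefined intervening factors to the resilience model. If the rule is followed on its natural reading, the result may no longer be the total effect of hypnotherapy on resilience.

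The documents give neither the lifestyle shift nor the mediated share, so the loss cannot be fixed. Over the assumed range it runs from almost nothing (0.3 SD shift, no mediation) to about 5 to 6 of the 21.6 points, with power near 0.64 instead of 0.89 (0.8 SD shift, 30% mediated, 22 per arm). If nothing acts through lifestyle there is no bias, only some loss of power. The documents do not support saying that the effect will be reduced, only that the rule as written allows it.

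**What to change.** - In 2.13 and 2.15, limit covariates in all between-group analyses to variables measured before randomisation, and replace *intervening factors* in 2.13 with *baseline factors*. Section 2.10 hands out the first questionnaires after allocation, so state how baseline is defined for those scores.
- Report diet and exercise recorded during treatment by arm, as adherence or process data. If they are to be modelled, do so only in a separately labelled exploratory mediation analysis.
- Separately, reconcile the three statements on diet and exercise: the recommendation in 2.10, the requirement to keep the regular routine in 2.15, and session five in Table 1.

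The cost is wording, plus the documentation and ethics approval that 2.12 requires for a change in study methods. No new data and no extra participants are needed. The article reports that sampling is still under way, so on that account the change can be made before analysis.
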